### Procedure For Unblinding If Needed {17b}

Overall, the study has very minimal risks, and by its nature participants may know which intervention they/their building is receiving based on what services, if any, are provided and what materials are displayed, if any. Blinded data collectors may also guess the intervention based on what materials are displayed or not displayed. The intervention team, the peer educators will report any serious adverse events that occur during intervention implementation to the research team, but the identity of the participant and the intervention assigned to their building will not be revealed to data collectors.

## Data collection and management

### Plans For Assessment And Collection Of Outcomes {18a}

There are three assessments during this trial. These include a baseline assessment conducted upon recruitment and after building randomization, an interim assessment conducted over the phone approximately 3 months after the delivery of intervention, and a final long-term assessment conducted approximately 12 months after the delivery of intervention. The survey questionnaire collects information on housing conditions, indoor air quality, personal smoking behavior and cessation attempts, exposure to secondhand smoke, opinions on secondhand tobacco exposure, the smoke-free policy and tobacco policies, and health conditions. Additionally, passive drool samples from 25% of participants (n = 128) is collected at the time of the baseline assessment and at the final follow-up. Sensory building observations occur at the start of recruitment and during the final assessments to record signs of active smoking and/or tobacco/marijuana odor. The presence of cigarettes, cigars, ashtrays with/out ashes, matches or lighters will be documented within apartments and around the building premises including stairwells, elevators, hallways, laundry rooms, in/outdoor community spaces, playgrounds, and the perimeter of the buildings.

### Plans To Promote Participant Retention And Complete Follow-up {18b}

We make every attempt to retain participants and minimize attrition bias through a range of rapport building and retention techniques, incentives, and cultural adaptation of study materials. Though primary outreach is conducted in-person, we also conduct mail and text outreach to maximize participant engagement. We have also powered the study based on 80% retention.

While the study presents minimal risks, participants may withdraw at any time upon request.

Alternatives available to participants outside the research context are simply not enrolling and attempting to serve the greater good by participating in other research or community service activities.

### Data Management {19}

We will use a digital data capture system and collect data on password-protected laptop computers. Specifically, this multi-user system is registered with CUIMC IT. Data will be transferred, encrypted, backed-up and transferred to the data manager who will review the forms daily for completeness.

Data will be transferred via a firewall-protected, secure, electronic file-transfer to computer server space dedicated to the proposed study and protected with firewall and encryption technologies. Only [name], the Project PI, will have master access to this server and she will be required to authenticate herself via password each time the data are accessed.

Because this study is funded by the National Institutes of Health (NIH), the study is automatically issued a federal Certificate of Confidentiality. It is possible that participants will disclose information during their participation in the study and/or interviews and focus groups that indicates their involvement in illegal activities or indicates illegal activities by others. A Certificate of Confidentiality is one further means of ensuring that this information is kept confidential. Should participants disclose information in the middle of an interview that clearly indicates that they or those around them are in imminent danger, the interview will be suspended and 9-1-1 will be contacted.

Personally identifiable information (PII) will be collected and entered into an electronic database for each study participant. This PII data will be necessary to the conduct of the proposed trial and include: name; street address, city, county, and zip code; telephone numbers; and possibly electronic mail addresses. All data will be specifically used for the purposes of the proposed research. No PII will be disclosed to anyone who is outside of the proposed research team and all PHI will be destroyed when the study is concluded. We will institute strict precautions and security procedures to maintain data integrity and confidentiality:

All data will be stored on a centralized computer server at the Columbia University Mailman School of Public Health. This server will be dedicated to the proposed study and will be protected with up-to-date “fire-wall” electronic security technology.Only [name], the Project PI, and the Project Coordinator will have master access to this server and the data.Computer administrators, co-investigators, a project manager, project coordinators, and laboratory staff will only be granted data access at the discretion of the Principal Investigator. Furthermore, this access will only be granted as needed for finite periods of time throughout the study.On a regular daily basis, laboratory staff will destroy any “portable” data (including both electronic and paper copies) that are transferred from external data sources to the university computer server.Once all records are linked and compiled into a single database, any and all PII identifiers will be destroyed.

The PI and the project coordinator will be responsible for providing and documenting appropriate user access to the study database and preventing against major sources of data security problems: unauthorized internal access to data, external access to data, and malicious intent to destroy data and systems. This user access will ensure that only appropriate and authorized personnel are able to view, access, and modify trial data.

Modifications to data will be performed in a manner that documents data modification, user access associated with modification, data associated with modification, and values prior to modification. The PI and the project coordinator will also be responsible for optimizing database performance, reliability and backup of data. External, unauthorized access to data is prevented through cooperative efforts of the PI, the project manager, and network and systems administrators. Highly successful measures will be employed through network firewall technologies to prevent unauthorized external access to data repositories.

### Confidentiality {27}

We will establish excellent rapport with respondents and assure them that we are researchers with a private, local university and in no way representing NYCHA, law enforcement, or government agencies. No analyses, reports, or peer-reviewed articles will identify any participants. In later phases of the study, in-depth interviews may also be conducted somewhere nearby but not in the respondent’s household, such as a porch, church, park, café, etc., yet regardless of location all protections and confidentiality protocols will apply.

We will record information about the participant during initial participant recruitment that will allow us to recontact that same individual for follow-up surveys at 3 and 12-months post-intervention. With the participant’s consent, this information may include address and/or telephone number so that we can recontact them to schedule subsequent follow-up, possibly over the telephone. Participants will also be informed that any other identifying information that is recorded – such as names, birthdates, etc. – for study participants, will be destroyed at the conclusion of the study.

#### Plans for collection, laboratory evaluation and storage of biological specimens for genetic or molecular analysis in this trial/future use {33}

Exposure to smoke either directly among smokers or indirectly through secondhand smoke will be assessed through self-report and salivary collection.

We will collect saliva for 25% of recruited individuals from each building on a rolling basis at baseline and at 12 months via passive drool collection. Donors tilt their head forward, allowing the saliva to pool on the floor of the mouth, then pass the saliva through the SalivaBio Collection Aid (SCA) into a polypropylene vial. Collection protocols/methods are available online at www.salimetrics.com or upon request (Salimetrics Cotinine ELISA Kits). Saliva cotinine will be measured at the Columbia University Biomarker Core Laboratory directed by [name] using cotinine ELISA Kits (Salimetrics, State College, PA). The Salimetrics ELISA kit is an enzyme immunoassay used to measure primary or secondhand exposure to nicotine via cotinine. It is not intended for diagnostic use. It is intended only for research use among humans and some animals. The assay is non-invasive, involves no genetic sequencing, and is not used as a diagnostic procedure.

## Statistical methods

### Statistical Methods For Primary And Secondary Outcomes {20a}

We will conduct intent-to-treat (ITT) and contamination-adjusted intent-to-treat (CA-ITT) analyses to estimate the effects of the smoking relocation/cessation and resident endorsement interventions compared to the standard program implemented by NYCHA (no treatment). CA-ITT analyses will account for unanticipated contamination between trial arms and be completed via two-stage instrumental variables regressions using the original random allocation codes per assigned unit. Preliminary data analysis will include examination of distribution and summary statistics of all variables by intervention groups at each time point. The continuous variables with skewed distribution will be properly transformed, if necessary, to reduce impact of extreme values or improve model fitting. We will use box-plots to examine how distribution of a quantitative variable varies by categories of a categorical variable, and use scatter plots and Spearman correlation coefficient to examine bivariate associations between quantitative variables. Chi-square and Kruskal-Wallis tests will be used to detect group differences in categorical and quantitative baseline variables, respectively. For successful randomization, we expect no difference in the distribution of all baseline variables among the four arms. The baseline variables that differ by intervention groups and are related to outcomes of interest will be controlled in the aim specific models.

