### Trial design {8}

The trial design is a borough-stratified, four-arm, factorial-design, cluster RCT that targets 64 randomly selected buildings (16 buildings per arm) in separate NYCHA developments. We are recruiting and following 8 randomly selected residents stratified by smoking status − 4 smokers and 4 non-smokers - per building (n = 512) into four arms: (1) reduction/cessation, (2) resident endorsement, (3) reduction/cessation plus resident endorsement and (4) the standard approach (128 participants per arm) as shown in Fig. 1. A partnering community-based organization, Health People, Inc., specializing in peer-to-peer health education will train and supervise peer educators (PEs) who will then deliver the designated interventions. Quantitative assessments via survey questionnaire, salivary cotinine measurements, as well as sensory building observations will be used to measure outcomes. We will be evaluating the efficacy of compliance support interventions in reducing personal smoking and exposure to second-hand smoke in public housing. In addition, we will also determine if the tobacco retail environment surrounding a given public housing building moderates the relationship between compliance support interventions and smoking-related outcomes.

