## Assignment of interventions: allocation

### Sequence Generation {16a}

A list of eligible buildings from each borough will be randomly ordered by computer-generated random numbers for each borough. Then, the first 24 buildings for each borough (n = 48, 24 per borough) will be randomly assigned to receive intervention A, B, or A + B.

Additionally, all buildings that are eligible for the study but have been identified by NYCHA as locations where they will conduct activities to promote the smoke-free policy will be randomly ordered by computer-generated numbers for each borough. Then, the first 8 buildings for each borough (n = 16, 8 per borough) will be assigned to serve as a control site.

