### Primary outcome

1)

Self-reported average number of cigarettes smoked per day and secondhand smoking exposure (hours of secondhand smoke exposure in the building in the past 7 days) will be measured at baseline (in person interview), 3 months (phone interview) and 12 months (in person interview). Salivary cotinine will be measured for 25% of the sample at baseline and at the 12-month follow-up for smokers to evaluate reliability of self-reported smoking behavior in Aim 1 and for non-smokers to evaluate self-reported secondhand smoke exposure in Aim 2.

To examine the intervention group differences in the change of self-reported smoking (Aim 1), we will use GLMRM with identity link, E(Yijkh) = ßh + ßkhtk + ßZij, where Yijkh is an outcome variable (transformed if necessary) for smoking exposure measured at time tk (t0 = 0 for baseline; t1 = 1 for 6 months, 0 else; and t2 = 1 for 1 year, 0 else) from the ith participant of the jth building in the hth arm/group (h = 1, 2, 3, 4). For the reference group of h = 4, ßk4 = 0 for k = 0, 1, 2; so that parameter ßkh (k = 1, 2; h = 1, 2, 3 for intervention arm) indicates the difference in outcome change since baseline between intervention group h and reference group, and ß is a vector of coefficients for the vector of control variables Zij (if any). To examine if effect of treatment A depends on treatment B or vice-versa, we will test null hypothesis ßk1 = ßk2 + ßk3 for all k, which suggests independent effects of treatment A and treatment B and simpler model that E(Yijk) = ß0 + ß1A + ß2B + ßk0tk + ßk1tk A + ßk2tk B + ßZij with dummy variables A and B indicating treatment type. To examine the intervention group differences in the change in hours of secondhand smoke exposure in the building in the past 7 days for non-smokers, we will use GLMRM with log link (Aim 2). Models will be run with and without control variables (if any).

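### Covariates are chosen by baseline significance tests that ignore building allocation; the rule cannot pick borough, and the change model gives up precision that baseline adjustment would recover

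*Protocol article*

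**What the plan says.** All references are to the protocol article.

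- **Statistical Methods For Primary And Secondary Outcomes {20a}**: "Chi-square and Kruskal-Wallis tests will be used to detect group differences in categorical and quantitative baseline variables, respectively". The section adds "For successful randomization, we expect no difference in the distribution of all baseline variables among the four arms" and then gives the selection rule: "The baseline variables that differ by intervention groups and are related to outcomes of interest will be controlled in the aim specific models". No test level is stated.
- **Trial design {8}**: the trial is a "borough-stratified, four-arm, factorial-design, cluster RCT" with 64 buildings, 16 per arm, and "8 randomly selected residents stratified by smoking status" in each (four smokers, four non-smokers).
- **Sequence Generation {16a}**: "the first 24 buildings for each borough (n = 48, 24 per borough) will be randomly assigned to receive intervention A", B or A+B. Control buildings are the first eight per borough from a separate list of sites that the housing authority chose for its own programme.
- **Aim Specific**: estimation is by GEE, which allows for correlation within building and within person.
- **Primary outcome**: each arm has its own baseline intercept, the effect of interest is the arm-by-time term, and control variables enter as a time-constant vector that may be empty. Then: "Models will be run with and without control variables (if any"). Neither version is named primary.
- **Explanation For The Choice Of Comparators {6b}**: one covariate is named in advance, participation in the housing authority's programme. Borough is named in no model.

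**The concern.** Three features of the covariate plan work against each other.

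1. The screening tests treat residents of one building as independent, while arms are assigned to buildings. They therefore reject too often under the null, and the set of adjustment variables is partly a product of chance.
2. A variable enters only if it differs between arms. Stratification is meant to make borough not differ, so the rule excludes the one factor that the design says matters.
3. The model spends the baseline measurement on a raw change from baseline with unconstrained arm means. For arms that were randomised against each other this is less precise than conditioning on the baseline value.

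At stake are a covariate set that cannot be known before the data are seen, a headline estimate left open between two versions, and precision lost even if the plan is followed exactly.

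**Working it through.** **Check of the clustering inputs.** The sample size section uses intracluster correlations (ICC) of 0.1, 0.15 and 0.2 and four subjects per building. With design effect DEFF = 1 + (m − 1) × ICC, the detectable effect is (1.960 + 0.842) × √(2 × DEFF / n). For m = 4, ICC = 0.1 and the stated n = 256 per group, this is 2.802 × √(2 × 1.3 / 256) = 0.282 SD, against 0.283 stated. The plan's own power formula thus allows for clustering in the way its screening tests do not. (Whether 256 per group agrees with the number of buildings is a separate matter.)

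**False-flag rate of the screening tests.** A four-arm comparison has 3 degrees of freedom and a 5% critical value of 7.815 (level assumed). If clustering is ignored, the statistic is inflated by about DEFF, so the rate is P(χ²₃ > 7.815 / DEFF).

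| ICC | DEFF, m = 4 | Rate | DEFF, m = 8 | Rate |
|---|---|---|---|---|
| 0.02 | 1.06 | 6.1% | 1.14 | 7.7% |
| 0.05 | 1.15 | 7.9% | 1.35 | 12.2% |
| 0.10 | 1.30 | 11.1% | 1.70 | 20.4% |
| 0.15 | 1.45 | 14.5% | 2.05 | 28.3% |
| 0.20 | 1.60 | 18.1% | 2.40 | 35.4% |

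Simulated Kruskal-Wallis tests (4 arms × 16 buildings, 4,000 data sets) gave 11.0%, 13.9% and 17.8% for m = 4, and 19.6%, 25.9% and 34.1% for m = 8, at ICC 0.1, 0.15 and 0.2. With ten independent candidates (assumed), that is about 1.1–1.8 or 2.0–3.5 chance flags, where a valid test gives 0.5. The filter on relation to outcome then removes some of them.

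**Borough.** Twenty-four intervention buildings per borough over three arms is 8 per arm per borough if split equally, and the control arm also has 8 per borough. Each arm is then half from each borough, so a test for a difference between arms has nothing to find.

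**Baseline value, randomised arms, one follow-up.** Let R be the correlation between the baseline and follow-up building means. A change score has variance proportional to 2(1 − R), and the best baseline adjustment has 1 − R². Their ratio is (1 + R)/2, so the reduction is (1 − R)/2. Take within-person correlation ρ = 0.3, 0.5, 0.7 (assumed), ICC 0.1 and four residents per building.

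- If building effects correlate over time as persons do, R = ρ and the reduction is 35%, 25%, 15%. Simulation gave 14–34%.
- If building effects persist fully, R = (0.1 + 0.225ρ) / 0.325 = 0.515, 0.654, 0.792 and the reduction is 24%, 17%, 10%. With an individual-level slope, simulation gave 9–23%.
- At ICC 0.2 with full persistence, R = (0.2 + 0.2ρ) / 0.4 = 0.65, 0.75, 0.85 and the reduction is at most 17.5%, 12.5%, 7.5%.

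**Does the rule damage the main contrast?** The linear repeated-measures model was simulated with building-robust standard errors (2,000 data sets per setting).

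- *Complete data:* rule-selected covariates, or a borough main effect, changed the 12-month change contrast and its standard error by less than 10⁻¹⁵. The error rate was 5.6% in each case.
- *20% random dropout:* error rates were 4.9–5.2% in all models. The rule moved the estimate by 0.006 on average and 0.071 at most, against a standard error of about 0.20.
- *Borough shifts the change by 0.5 SD:* the mean standard error was 0.197 against a true SD of 0.178 (error rate 3.8%). With borough × time it was 0.173 (5.9%).
- *Borough shifts the change by 0.3 SD:* the error rate was 4.1% without borough × time and 5.2% with it.

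**The case against.** A reader might infer that the selection rule and the missing borough term make the reported error bars wrong. The documents do not support that for the main linear contrast. GEE deals with clustering, and a time-constant covariate entered as a main effect drops out of the arm-by-time term when data are complete. The same algebra covers the log-link model, though this was not simulated; for logit outcomes the cancellation is not exact. A borough difference in level drops out too. Only a borough effect on the change itself matters, and leaving that out makes the standard error too wide, which costs power and does not create false positives.

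A reader might also call every flagged difference spurious. That fails for the control arm, whose buildings come from a separate list and were not randomised against the others. Differences from it may be real confounding.

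Other points on that side carry some weight. The primary models use four residents per building, so the rates for eight apply only if screening pools smokers and non-smokers, which the text does not settle. The ICCs of 0.1–0.2 are outcome values and may be too high for baseline variables. Change from baseline by GEE is a recognised analysis, so that part concerns efficiency. Naming borough and the primary version could sit in an analysis plan that is not shown.

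What the objection does not remove is the test-based rule itself, which the article states outright and which by construction passes over borough. Nor does the cancellation rescue the rule: where it is exact, the adjustment does nothing about the imbalance it is meant to correct.

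**Conclusion.** The concern holds as a fault in covariate selection and a loss of precision. The screening tests flag roughly 11–18% of null variables at four residents per building and 19–35% at eight, assuming a 5% level and baseline ICCs of 0.1–0.2, or 6–12% across both cluster sizes at ICCs of 0.02–0.05. These rates precede the second filter. The rule cannot select the stratification factor. Among the randomised arms, raw change forgoes a variance reduction of about 9–34%, assuming ICC 0.1 and within-person correlations of 0.3–0.7, and less if building effects are larger and persistent. It does not amount to invalid inference on the main linear contrast. The change should be made, but the trial's conclusions do not stand or fall on it.

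**What to change.** - Delete the baseline significance tests as a way of choosing covariates; describe baseline balance without them.
- For comparisons among A, B and A+B, adjust the 3- and 12-month outcomes for the participant's own baseline value, or constrain baseline means to be equal across these arms, and include borough.
- Wherever the change model is kept, add borough × time, since a borough main effect alone leaves the change contrast unaltered with complete data.
- For contrasts with the control arm, list the confounders in advance on subject-matter grounds. Do not impose equal baseline means there.
- Name one model as primary and label the others, including the version without covariates, as sensitivity analyses.

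This is a change of wording that needs no new data and costs a few degrees of freedom.
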